
### Intervention

All participants sign an Informed Consent Form. The study was approved by the Ethics Committee of Nuestra Señora de La Candelaria University Hospital. The intervention (except for nutrition counseling), number of appointments and laboratory tests are the same in both groups.

Participants in the LFDI group are advised to eat a low-fructose diet designed on the basis of standard diets (1000, 1250, 1500, 1750, 2000, 2250, 2500 or 2750 kcal/day) recommended by the Canary Islands Health Service [18]. Low-fructose diets are designed by calculating free and total (free + fructose associated with sucrose) fructose contents in standard diets. Foods with a fructose content in the highest quartile for the amounts corresponding to the standard diet are removed from the standard diet. The format and graphical appearance of the information about the participant’s diet are identical in both groups. Physicians and nurses who prescribe the standard diets are unaware of which foods have been excluded from the low-fructose diets. To avoid contamination bias while recruitment is currently underway, the present report does not include information on the composition of the low-fructose diets.

Nutrition counseling and reinforcement take place at weeks 2, 4, 8, 12, 16 and 20. During this process we emphasize to participants the importance of involving in the intervention the person in the household who purchases and/or prepares food. At week 2, after the physician or nurse has reviewed the nutritional information, intervention via individualized nutrition counseling begins. At week 24 a second blood sample is obtained for analysis. Two weeks before week 24 the participants are given a new Information Pack containing the same materials as the initial Information Pack at the start of the study, with instructions on how to record foods and beverages consumed during 4 days (including one weekend day or holiday). On the day of the appointment to provide a new blood sample, the participant meets first with the physician or nurse to review their food diary in detail.

The schedule of enrollment, interventions and assessments, which is based on the Standard Protocol Items: Recommendations for Interventional Trials (SPIRIT) figure, is shown in Fig. 1 and the process for participant recruitment and follow-up is shown in Fig. 2.

**Fig. 1 Fig1:**
[figure not shown]
Schedule of enrollment, interventions and assessments

**Fig. 2 Fig2:**
[figure not shown]
Patient recruitment and follow-up process

#### Physical activity and dietary intervention in both groups

To determine leisure time physical activity we use the Minnesota Questionnaire which has been validated for the Spanish population [19, 20]. Participants are also asked about their physical activity at work. Physical activity is recorded for the week prior to the appointment and for the six previous months. If the participant reports physical activity equivalent to moderate or brisk walking for 150 min per week or more, they are encouraged to continue this level of activity. If less physical activity is reported, the participant in encouraged to devote 150 min per week to brisk walking.

When the research team receives the four daily food diaries and information on physical activity from the physician or nurse, team members analyze the information to make general dietary recommendations, and advise the health center staff member on the kcal/day the participant’s diet should contain, and on the type and amount of physical exercise to prescribe. To evaluate adherence to the prescribed diet, the physician or nurse is reminded to advise participants to record a 24-h recall of foods and beverages consumed at weeks 8, 12, 16 and 20. The kcal/day in the prescribed diet are calculated as 30 or 40% less than the kcal/day of the participant’s energy requirements for their ideal weight according to age, sex and physical activity. Ideal weight is calculated as the product of 25 multiplied by the square of height (measured in meters); physical activity is evaluated from information provided in the Minnesota Questionnaire, and participants are asked specifically about the nature of their employment. Members of the research team classify physical activity into four levels of intensity: mild, moderate, vigorous or very vigorous. Energy requirements in kcal/kg/day are calculated with the protocol for persons with obesity used by the Canary Islands Health Service (based on recommendations of Spanish Ministry of Health Guideline, 2008 [21]). For men, the requirements are assumed to be 42, 46, 54 and 62 kcal/kg/day, respectively, for each of the four levels of intensity, and for women the requirements are assumed to be 36, 40, 47 and 55 kcal/kg/day. These figures for energy requirements are reduced by 5% for participants 45 to 49 years old, by 10% for those 50 to 59 years old, and by 20% for those aged 60 years or older. After energy intake equivalent to 30 to 40% less than the individual’s energy requirements is calculated, the participant is advised to consume the diet that most closely approximates this figure (1000, 1250, 1500, 1750, 2000, 2250, 2500 or 2750 kcal/day). Additional file 3 provides an example of the standard 1750 kcal/day diet, how the energy requirements for the recommended diet are calculated and one example of the information provided by the researchers to participating physicians and nurses.

On the basis of the available data for the Canary Islands’ population, we decided that the energy intake restriction should ideally represent approximately 35% of each participant’s energy requirements. Mean energy intake in the general population of the Canary Islands is 2300 kcal/day [22]. The recommended diets for participants with obesity provide 1250 to 1500 kcal/day for women (mean 1350 kcal/day) and 1500 to 1800 kcal/day for men (mean 1650 kcal/day) [23]. The mean energy intake for men and women is, therefore, 1500 kcal/day. The difference between the mean energy intake of 2300 kcal/day in the Canary Islands’ population and the mean energy intake of 1500 kcal/day is 800 kcal/day, i.e., 35% of the daily energy consumption. This calculation is in agreement with the energy restriction of the 30–40% recommended by the above mentioned guideline [21].

Although we decided on a range of energy intake restrictions between 30 and 40% to match the prescribed diets as closely as possible to the individual requirements we calculated, in practice the restriction in the prescribed diets closely approximates 35% of the participants’ energy requirements.

### Data recording and analysis

A specifically designed Case Record Form (CRF) is used to record personal contact information, socioeconomic class, personal and family antecedents, and to compile data for 24-h recall food consumption and physical activity. The CRF is shown in Additional file 4. Socioeconomic class is stratified as low, middle and high according to the ICE method Incomes, Crowding index, Education [24] which has been weighted and validated for the Canary Islands’ population. Mean nutritional value of each of the four daily records is used as the baseline value (week 0), and is estimated mainly from the Mataix Spanish food composition tables for macronutrient, sugar and calorie intakes [25]. Blood samples are analyzed at the Canary Islands University Hospital Complex laboratory. Insulin is measured with a chemiluminescence immunoassay method and an Architect i2000SR immunoassay analyzer (Abbott Diagnostics). Glucose, total and HDL-cholesterol and triglycerides are measured with enzymatic methods (Cobas c602, Roche Diagnostics). Microalbumin/creatinine ratio is determined with an immunoturbidimetric method (Cobas c501, Roche Diagnostics). To measure TSH and T_4_ a chemiluminescence immunoassay is used with a Cobas e602 processor (Roche Diagnostics). The value for LDL-cholesterol is obtained with the Friedewald formula if triglycerides are below 400 mg/dL. Insulin resistance is estimated from fasting serum glucose and insulin concentrations with a computer-based Homeostasis Model Assessment system (HOMA2-IR) provided by the Oxford Centre for Diabetes Endocrinology and Metabolism [26] (http://www.dtu.ox.ac.uk/).

To normalize the methods used for measurements, data recording and intervention the research team met with all physicians and nurses who collaborate in the study 2 months before field work began. During a 7-h session team members explained the methodology and instructed the health center staff members in how to record data from the food diaries and how to implement the dietary interventions. All collaborating health center staff members were given a manual with photographs illustrating food item sizes, portion sizes and weights in order to minimize recording biases, and they were also given graphical material illustrating how to estimate the volume of different beverages. One year after the start of the recruitment a second meeting was held with all collaborating health center staff members to update them on the progress and results of the study thus far.

Data recording is handled by an externally contracted data manager whose fees are covered from funding for this study. Data analysis will be performed by the researchers, and no member of the entity responsible for fund management will participate in data recording or data analysis. No member of the entity responsible for fund management participated in the drafting, review or revision of this manuscript.

CRFs and food diaries are emailed to an account which is accessible only by three of the principal investigators and the data manager. All records are printed to facilitate study and are kept in a locked cabinet. The results of all laboratory analyses are sent in encrypted form by the laboratory head to the principal investigator, who then sends them personally to the individual physicians responsible for each participating patient at each health care center.

The data manager is specifically trained in transcribing the data from CRFs, laboratory reports and food diaries to the database used for statistical analyses (Statistical Package for the Social Sciences; see below under “Statistical analysis”). The data from CRFs, laboratory reports and food diaries are not exported digitally to the statistical software for two reasons. Firstly, funding limitations meant that the study could not commence until additional funding was obtained to cover the basic costs of the study. Secondly, the timeline for this study necessitates food diaries to be obtained and recorded (four during week 0 and four at week 24), and data entry from the diaries requires interpretation by the data manager, who is specifically trained to interpret the different types of foods and to use the correct unit of measurement for different food items (mass, volume, portion, etc.). However, every 15 days the accuracy of data entry was verified by checking all data entered in each of the databases against the original data sources.

### Monitoring

The research team is responsible for monitoring the study. At week 24 the participants are asked whether they had side effects from the prescribed diet (CRF). At the time of writing the only side effect reported by any participant was constipation. The research team is also responsible for systematically reviewing the causes of withdrawal or dropout. Because no experimental medications or foods are used in this study, we believe that there is no need to create a specific data monitoring committee made up of professionals who are not involved in the research per se.

### Statistical analysis

Before-after changes in IR, laboratory indicators and anthropometric values are determined with Student’s *t* test for paired samples. Comparisons between the intervention and control groups for variables indicative of IR are done with Student’s *t* test for independent samples when the frequency distribution is normal, or with the Mann-Whitney *U* test when the distribution is not normal. For these comparisons multiple linear or regression models are used as appropriate to detect possible confounders or independent prognostic factors for IR that are not controlled for in the trial design. Student’s *t* test for paired samples will be used to analyze changes between week 0 and week 24 in the main outcome variables in each group (HOMA2-IR, fasting blood glucose and insulin, and these same measures after an oral glucose overload) and the secondary outcomes (fasting LDL-cholesterol, HDL-cholesterol and triglycerides, and these same measures after a glucose overload; waist circumference, waist to height ratio, BMI and blood pressure). To verify compliance with the recommended diets the same analysis will be done for total calorie intake and individual nutrient intakes. These analyses will record results for the variables noted above between week 24 and week 48, and between week 0 and week 48. Student’s *t* test for independent samples will be used to analyze the differences between groups observed from week 0 to week 24 for the variables noted above. As potential confounders we will consider calorie intake, variations in nutrient intakes other than fructose, and physical activity. If differences are detected between groups at the start of the study in HOMA2-IR, any nutrient intake or physical activity, appropriate adjustment will be used in the outcomes analysis. An intention-to-treat analysis will be done taking into account losses to follow-up, and using the most recent changes and measurements available for participants who did not complete the study. All hypothesis tests will be two-sided with a significance level of *p* < 0.05, and all statistical analyses will be done with the NT Professional v. 21.0 (IBM) statistical package (SPSS) for PCs in a Windows environment. More specific information about the trial and protocol is summarized in the Standard Protocol Items: Recommendations for Interventional Trials (SPIRIT) Checklist (Additional file 5).

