### Design

A single-blind, multicenter, randomized controlled **f**ield trial with two groups of participants (low fructose/sucrose diet versus standard diet) recruited at primary care health centers in Tenerife island (Canary Islands, Spain). Sample size: because of the lack of consensus in the academic literature regarding the cutoff value of HOMA2-IR that defines the presence of IR, we opted to use body weight change. We estimated a mean weight loss of 4 kg (1.43 kg/m^2^ BMI assuming a mean height of 1.67 m for the Canary Islands’ population [16]), a significance level of *p* ≤ 0.05, 80% power and a 20% dropout/loss to follow-up rate. A weight loss of 4 kg was estimated based on maximum weight loss in the only interventional trial reported to date of the effect of lower fructose consumption on body weight and IR [15]. Dietary intervention trials aimed at studying weight loss have reported similar amounts of weight loss after 6 months [17]. In the trial reported here, in which both groups consume an isocaloric diet, we do not anticipate differences between the groups in the amount of weight lost. Based on these calculations our estimated sample size for each of the two groups is 245 participants.

The primary outcome measure is insulin resistance (IR) which is estimated from fasting serum glucose and insulin concentrations with the computer-based Homeostasis Model Assessment system (HOMA2-IR) at baseline, 24 and 48 weeks. The secondary outcomes are BMI, waist circumference (waist to height ratio) and blood pressure which are measured at baseline, 4, 8, 12, 16, 20, 24 and 48 weeks, and total cholesterol, HDL-cholesterol, LDL-cholesterol and triglycerides which are measured at baseline, 24 and 48 weeks.

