### Randomization

Participants are randomized by health care zone. Patients in the low-fructose diet intervention group (LFDI) are assigned to health centers in the western zone of Tenerife island, and patients in the Canary Islands Health Service standard-diet control (SDC) group are assigned to the eastern zone of the island. This randomization system is used to prevent contamination bias. If patients randomized to both groups attended the same health center this source of bias would be difficult to avoid because many patients in the LFDI group are likely to have relatives or friends in the SDC group, and vice versa. Contamination could also occur between staff members at a given health center. Sixteen primary health centers are participating in this study; all of them belong to the same health care administration district (Gerencia de Atención Primaria de Tenerife). Given that the total area of the island of Tenerife is relatively small, the characteristics of the population served by all health centers are assumed to be similar. The longest distance between participating health centers is 64 km. All centers and staff provide the same suite of services. The variations between centers in the catchment population assigned and the numbers of patients under each staff physician’s and nurse’s care are similar. We therefore do not anticipate between-group differences in the baseline data or systematic biases in the results of the care provided at different centers.

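### Diet is allocated by health zone across 16 centers, but the between-arm tests treat patients as independent, so the 5% level fails for any positive within-center correlation

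*Protocol article*

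**What the plan says.** Under Randomization, the protocol article states "Participants are randomized by health care zone". Low-fructose patients "are assigned to health centers in the western zone of Tenerife island", while patients in the standard-diet "group are assigned to the eastern zone of the island". No center delivers both diets. The section adds "Sixteen primary health centers are participating in this study" but does not say how many lie in each zone. The reason given is contamination among relatives, friends and staff: "This randomization system is used to prevent contamination bias". The section expects no baseline differences because "the characteristics of the population served by all health centers are assumed to be similar".

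Under Statistical analysis, "Comparisons between the intervention and control groups for variables indicative of IR are done with" Student's t test for independent samples, or Mann-Whitney when the distribution is not normal. Regression models are added for confounders, and the ones named are calorie intake, nutrients other than fructose, and physical activity. No center term, random effect, cluster-robust error or center-level analysis is specified.

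The sample size under Design rests on a 4 kg weight loss, a 0.05 significance level, "80% power and a 20% dropout/loss to follow-up rate". It mentions neither an ICC nor a design effect.

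**The concern.** The diet was assigned to groups of patients, so the independent unit is at best the center. Patients at one center share the physicians and nurses who counsel them, review their food diaries and take their measurements, and they share a local population. The protocol itself treats links among patients and staff of a center as strong enough to rule out individual allocation. An independent-samples test assumes that those links leave no trace in the outcomes.

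If they do leave a trace, the test counts 392 to 490 independent observations where there are fewer. The primary comparison of change in HOMA2-IR, and every other between-arm comparison, would then be declared significant too often. The Discussion proposes carrying a positive result into routine care, so a false positive has consequences.

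**Working it through.** **Inputs from the protocol.** 245 per arm (490 in total), 20% loss, 16 centers, two-sided 5% test.

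**Inputs assumed.** 8 centers per arm, equal center sizes, and ICC of 0.01, 0.02 or 0.05. The protocol supplies none of these.

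**The plan's own figure.** 245 × 0.8 = 196 evaluable per arm. Using n = 2(1.96 + 0.8416)² SD² / d² with d = 4 kg, 196 per arm requires SD = 4 × √98 / 2.8016 = 14.1 kg. If loss was instead added as n × 1.2, then n = 204 and SD = 14.4 kg. No SD is stated, so 245 can be neither confirmed nor refuted. Nothing in the stated inputs allows for clustering.

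**Cluster size.** After loss, 392 / 16 = 24.5. If all patients are kept, 490 / 16 = 30.6.

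**Formulas.**
- Design effect: DE = 1 + (m − 1) × ICC.
- Actual type I error of the patient-level test: 2 × [1 − Φ(1.96 / √DE)].
- Width of a valid center-level interval relative to the patient-level one: √DE × 2.145 / 1.966. These are the critical values on 14 df (16 centers − 2) and 390 df; their ratio is 1.091.

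**Results with m = 24.5.**

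| ICC | DE | √DE | Type I error, formula | Type I error, simulated | Interval wider by |
|---|---|---|---|---|---|
| 0 | 1.00 | 1.00 | 5.0% | not run | 9% (df only) |
| 0.01 | 1.24 | 1.11 | 7.8% | 7.5% | 21% |
| 0.02 | 1.47 | 1.21 | 10.6% | 9.8% | 32% |
| 0.05 | 2.18 | 1.47 | 18.4% | 18.6% | 61% |

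Example at 0.02: DE = 1 + 23.5 × 0.02 = 1.47; 1.96 / 1.212 = 1.617, two-sided tail 10.6%; 1.212 × 1.091 = 1.32.

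The simulation used 20,000 null trials with 8 + 8 centers of 24 or 25 patients. A t test on the 16 center means (14 df) rejected in 4.9%, 4.8% and 5.1% of them, so it held its level.

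**If carrying forward the last measurement keeps all 490 (m = 30.6).** DE is 1.30 / 1.59 / 2.48 and the type I error 8.5% / 12.0% / 21.3%. With critical values 2.145 and 1.965, intervals widen by 24% / 38% / 72%.

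**What a center-level analysis cannot reach.** The simulation was repeated with an assumed between-zone variance of 0.5% of the total. The patient-level test then rejected in 19% / 21% / 28% of null trials, and the center-means test in 13% / 12% / 10%.

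**The case against.** The best defence is that center effects may be small. One laboratory analyses all samples, the research team advises on each patient's calorie level, staff had common training, and the populations are assumed similar. These features may well lower the ICC, and nothing in the protocol supports a value as high as 0.05. They do not show it to be zero. Similar populations also do not remove correlation that arises from shared counsellors and measurers. The size of the problem is therefore open, but its direction for any positive ICC is not.

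A second defence is that an article condenses a fuller plan. That would excuse silence. Here the test is named, and it does not fit the allocation described in the same article.

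Three stronger readings are tempting but unsupported:

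- *A center-level model makes the inference fully valid.* It does not. One zone was allocated to each arm, and such a model treats 16 centers as if each had been allocated independently.
- *The trial's power for its primary endpoint falls from 80% to a specific lower figure.* The 80% belongs to a 4 kg weight loss with no stated SD, and the protocol expects no difference in weight loss between arms. It states no between-arm effect for HOMA2-IR. A number can be back-solved, but it would not be the power of the primary comparison.
- *The p-values are certainly too small.* That holds only if the ICC is above zero.

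**Conclusion.** The point stands. The analysis named in the protocol does not match its unit of allocation, and the stated 5% level is not protected. Under the assumed 8 + 8 split, 24.5 completers per center and ICC of 0.01 to 0.05, the actual type I error is about 8% to 18%, and center-level intervals would be about 21% to 61% wider. Both are somewhat higher if all 490 patients are analysed. The figures depend on the assumed ICC; the mismatch does not. Because it affects the primary comparison and all other between-arm comparisons, it should be corrected before the data are analysed.

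Two limits belong with this conclusion. The correction deals with clustering by center and cannot separate diet from zone. The sample-size statement contains no stated allowance for clustering, but its 80% power cannot be restated for HOMA2-IR from the inputs given.

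**What to change.** Specify the primary between-arm analysis as a linear mixed model for change in HOMA2-IR from baseline to week 24, or for week-24 HOMA2-IR adjusted for baseline. Diet is a fixed effect and health center a random intercept, with small-sample degrees of freedom such as Satterthwaite. The alternative is a t test on baseline-adjusted center means, with 14 df. The two need not agree when center sizes differ, so name one as primary in advance. Center cannot be a fixed effect, because centers are nested within arms and would absorb the diet difference.

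Use the same approach for the other between-arm comparisons, report the number of centers per zone, and report the estimated ICC.

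Add two statements. First, with one zone per arm, zone and diet are fully confounded and no analysis can separate them, so any conclusion about diet carries that limitation. Second, the sample size made no stated allowance for clustering.

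The cost is wording. Center is already known for each patient, no new data are needed, and the named statistical package fits mixed models. The price is wider intervals and less apparent power; even at an ICC of zero, moving to 14 df widens intervals by about 9%. The zone limitation remains whatever model is used.

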## Discussion

The aim of this study is to evaluate the effectiveness of a low-fructose/sucrose diet compared to a standard diet in lowering IR in obese patients without DM after an intervention period of 24 weeks. Overall reductions in fructose/sucrose consumption are evaluated with no distinction between added sweeteners and sugar naturally present in foods. A diet low in foods with natural fructose content is prescribed for the intervention group, but participants in both groups are instructed to refrain from consuming foods with added sugar. This approach is used because it reflects the usual care offered at participating health centers, and in an effort to ensure comparable food intakes in kcal/day in both groups. To evaluate the difference in fructose intake our reference is the mean value from four daily food diary records from the end of the intervention period (week 24) compared to four daily food diary records at week 0. Although the evidence at present is insufficient to claim that four food diaries are sufficient to provide a reliable analysis of fructose or sucrose intakes, most studies that have estimated these intakes to date have used 24-h recall or (usually four) food diaries [27].

At present, the amount of fructose intake that could be harmful to health is unknown. A trial such as this one, carried out in the primary care setting, should provide valuable information for future efforts to control IR. Because the restricted calorie diet prescribed for our participants is similar in both groups, we expect to see similar weight reductions in both. Our hypothesis is that under our trial conditions, the reduction in IR will be greater in the group with the low-fructose diet than in the SDC. Accordingly, if the dietary intervention being tested, i.e., a diet low in fructose/sucrose, is able to reduce IR, the results – if translated into regular clinical practice – could provide a hitherto unavailable tool to prevent type-2 DM.

A potential limitation of this type of study is the likelihood that many participants will under-report some of their food intakes, as has been shown for persons with obesity. We will analyze the energy intake:basal metabolic rate ratio with a cutoff value of 1.16 for women and 1.19 for men to determine whether participants are under-reporting any food intakes [28].

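### Compliance with the diets is checked as change from week 0, not as agreement with the prescribed intake

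*Protocol article*

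**What the plan says.** In Statistical analysis, the outcome variables are analysed by a t "test for paired samples will be used to analyze changes between week 0 and week 24 in the main outcome variables in each group". The next sentence carries this over to diet: "To verify compliance with the recommended diets the same analysis will be done for total calorie intake and individual nutrient intakes". For fructose, the Discussion uses the same baseline reference: "our reference is the mean value from four daily food diary records from the end of the intervention period (week 24) compared to four daily" diary records at week 0.

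The prescription is set differently. Under Physical activity and dietary intervention in both groups, the research team takes 30 to 40% off each participant's energy requirement at ideal weight (25 times height squared), given age, sex and activity, and assigns the nearest of eight diet levels. Week 0 intake does not enter that formula.

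Three other statements bear on the point:
- Statistical analysis later plans a between-group comparison: "test for independent samples will be used to analyze the differences between groups observed from week 0 to week 24 for the variables noted above".
- The dietary intervention section collects further data: "To evaluate adherence to the prescribed diet, the physician or nurse is reminded to advise participants to record a 24-h recall" at weeks 8, 12, 16 and 20.
- The Discussion expects under-reporting and plans an energy intake:basal metabolic rate check.

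**The concern.** Compliance with a prescribed diet means agreement between what was eaten and what was prescribed. For energy, the prescribed figure exists for every participant, yet the stated check does not use it. A within-group test against week 0 asks only whether mean intake moved, and with about 200 people per arm a small movement suffices.

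The reference can mislead in both directions. A group starting far above its prescription can fall significantly and still be well short of it. A participant whose week 0 intake is already at the prescribed level complies without any change.

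The primary objective is an effect of fructose independent of calorie reduction, so a reader of the results will want to know how closely each arm followed its diet. A significant fall from baseline offered as verification would overstate what is known.

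**Working it through.** **Inputs**
- Arm size (Design): "our estimated sample size for each of the two groups is 245 participants", with 20% loss. Completers: 245 × 0.80 = 196.
- Test level (Statistical analysis): "All hypothesis tests will be two-sided with a significance level of" p < 0.05.
- Average energy cut (dietary intervention section): 2300 − 1500 = 800 kcal/day. The plan's percentage reproduces: 800/2300 = 34.8%, stated as 35%.
- SD of individual change in reported energy intake: not in the document. Assumed range 400 to 1000 kcal/day.

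**Step 1. Smallest observed mean fall that is significant.** Formula: t(0.975, 195) × SD/√196 = 1.972 × SD/14.

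**Step 2. True mean fall detected with 80% power**, from the noncentral t distribution with n = 196.

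| Assumed SD (kcal/day) | Significant at (kcal/day) | Share of 800 | True fall for 80% power (kcal/day) | Share of 800 | Remaining gap (kcal/day) |
|---|---|---|---|---|---|
| 400 | 56 | 7% | 80 | 10% | 720 |
| 600 | 85 | 11% | 121 | 15% | 679 |
| 800 | 113 | 14% | 161 | 20% | 639 |
| 1000 | 141 | 18% | 201 | 25% | 599 |

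The last column is 800 minus the true fall. It is roughly what a comparison with the prescription would show in a group starting at 2300 and prescribed 1500. If all 245 per arm were analysed, the significance thresholds would be 50 to 126 kcal/day (6% to 16% of 800).

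**Step 3. Distance between baseline and prescription.** By the protocol's formula, a man of 1.67 m, under 45, with mild activity requires 25 × 1.67² × 42 = 2928 kcal/day. A 30 to 40% reduction gives 2050 to 1757. Against a week 0 intake of 2300, the required change is 250 to 543, not 800. If his week 0 intake were already in the prescribed range, it would be zero. Change from week 0 therefore has no fixed relation to compliance.

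**Step 4. What the between-group test adds.** With 196 per arm it detects (1.960 + 0.842) × √(2/196) = 0.28 SD with 80% power. As an illustration with assumed values, let fructose fall by 15 g in the control arm and 25 g in the low-fructose arm, with SD of change 15 to 30 g. The paired test is significant in both arms with power of about 1.00, and the between-group test has power 0.91 to 1.00. If fructose falls by 15 g in both arms, the paired test again passes in both, but the between-group test is positive only at its nominal error rate. Separation can thus be judged from the between-group test. Neither test uses the prescribed amount.

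**The case against.** The strongest reply concerns the contrast between arms. Since both arms share the energy restriction and "participants in both groups are instructed to refrain from consuming foods with added sugar", fructose should fall in both. A reader might infer that the plan cannot tell the low-fructose diet from the standard one and would pass off a failed contrast as a true null effect of fructose. The document does not support that. The independent-samples test comes after the intake sentence and covers the variables noted before it, which naturally includes intakes, and step 4 shows that it discriminates. Only the slightly loose wording of its scope remains.

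Further replies have weight:
- No rule equating p < 0.05 with compliance is stated, and a paired analysis also yields the mean change, so a small fall would be visible. This stands, but the mean change is still measured from the wrong reference.
- The 800 kcal/day is a population-average rationale. This also stands: against the 250 to 543 kcal/day of step 3, a fall of 56 to 141 is a larger share, from 10% (56/543) to 56% (141/250).
- No gram target for fructose is shown. The Intervention section describes calculating fructose in the standard diets and removing top-quartile foods, and diet composition is deliberately withheld. The claim is therefore firm for energy only.
- Stable under-reporting partly cancels in a change from week 0 but not in a comparison with the prescription. This is a real cost of the alternative.
- The week 8 to 20 recalls are collected for adherence. How they are analysed may be left to the full protocol, and its absence here is no fault.

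**Conclusion.** The point holds in a limited form. The protocol fixes a method for verifying compliance, and that method uses the wrong comparator: it measures change from week 0, whereas the energy prescription is a known figure derived independently of week 0. At 196 per arm, significance is a weak standard. It is reached at an observed mean fall of 56 to 141 kcal/day, or 7% to 18% of the protocol's average cut, and a true fall of 10% to 25% of that cut gives 80% power. These figures rest on assumed SDs of 400 to 1000 kcal/day and on the 800 kcal/day average; the comparator problem depends on neither.

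The between-group test can address dietary separation but not adherence to the prescription. The matter concerns a supporting analysis and does not alter the HOMA2-IR comparison.

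**What to change.** In Statistical analysis, replace the compliance sentence with wording to this effect:
- For each participant, compute recorded minus (or divided by) prescribed kcal/day at week 24, and report the mean and 95% CI by arm. Read it alongside the energy intake:basal metabolic rate check already planned in the Discussion.
- Do the same for fructose only where the assigned diet has a calculated fructose content.
- Name the between-arm difference in week 24 fructose intake, adjusted for week 0 and with its 95% CI, as the measure of dietary separation. This also removes doubt about whether the between-group test covers intakes.
- Keep the paired change from week 0 as description.

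The cost is a wording change and a little more analysis, since the prescribed kcal levels and week 24 diaries are already part of the trial. The main drawback is that self-report bias acts directly on the comparison with the prescription: people who under-report can look compliant, so the result should not be presented without the under-reporting check.
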